## **OBJECTIVES**

In this 2-year multicentre, randomized integrated disease management program, we shall use a web-based disease management program to guide comprehensive assessment with or without risk stratification and clinical protocols and to compare the effectiveness of the JADE (structured care) versus DIAMOND Programs (usual care) in

- 1) reducing all diabetes-related clinical endpoints
- 2) control of multiple risk factors
- 3) improving quality of life, psychological well-being and health behaviors.

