### Intervention – JADE Group

In the JADE group, the patients are managed by a team of doctor, nurse and HCA, who share different tasks ranging from clinical diagnosis, education, data management and treatment to targets in order to improve the logistics in delivering this complex care protocol, augmented by information technology.

[figure not shown]

- 1) Patients randomized to the JADE group will be followed according to the protocol based on their risk levels. In addition to the CA visit, all subsequent FU visits will be documented followed by data entry into the JADE portal with issue of reports to both patients and doctor to promote sharing of information and informed decisions.

| Risk stratification                           | Very-high risk
4                                                 | High risk
3 | Medium risk
2 | Low risk
1 |
|-----------------------------------------------|---------------------------------------------------------------------|----------------|------------------|---------------|
| Cardiovascular renal complication             | ≥ 1                                                                 | 0              | 0                | 0             |
| Any risk score                                | NA                                                                  | ≥ SP           | ≥ ST and < SP    | < ST          |
| Stratification parameters                     | NA                                                                  | ≥ 3            | 2                | 0-1           |
| eGFR                                          | NA                                                                  | < 60           | 60-90            | ≥ 90          |
| Recommended number of medical visits per year | 6 or more                                                           | 4 or more      | 3 or more        | At least 2    |
| Comprehensive assessment                      | Every 12-18 months                                                  |                |                  |               |
| Other recommendations                         | Counselling/laboratory tests/telephone calls between medical visits |                |                  |               |

Parameters for risk stratification:

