- 3) If not yet put in place, the nurse/HCA will prepare a clinic folder for each patient and create a system to facilitate appointment booking and tracking of default.
- 4) Patients are booked for reviews led by the doctor-nurse-HCA team every 2-4 months, preferably in a setting different from the busy clinics in order to facilitate group education and promote peer support.
- 5) Between each FU visit, the nurse or HCA will contact the patient by phone or email to remind them of the appointments (e.g. medical FU visit or laboratory tests), adhere to medications and healthy lifestyles, perform self glucose monitoring and provide psychosocial support, as appropriate.
- 6) Before each FU visit, the nurse will ensure all tests (e.g. HbA1c, lipids, blood haemoglobin, renal function etc) ordered by the doctor are available in the folder for decision making.
- 7) At each FU visit, the patients will first see the nurse for record of BP, body weight and blood glucose (or HbA1c) as appropriate and enter them in the CRF. Patient's compliance will also be checked at each visit.
- 8) After the FU visit, the patients will see the nurse to clarify any issues and concerns. The nurse will reinforce compliance and record any changes in medications and note any procedures or tests ordered by the doctor. As and when appropriate, the nurse will remind doctors on action items prompted by the JADE e-portal, if omitted.
- 9) After each FU visit, the nurse will issue summary reports to be given to patients and doctors to promote sharing of information.

10) The FU and CA reports can be given to the patient on the same day of the visit or emailed or sent by post to patient as appropriate.

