#### Intervention - DIAMOND group

Patients randomized to the DIAMOND group will receive usual care after the initial CA with repeat CA at 12 and 24 months.

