|          |                     | 19%            | cataract        |
|          |                     | 37%            | microvascular   |
|          |                     | 43%            | PVD             |

| Steno 13 year FU       | SC=80 | UC=80 | HR   |
|------------------------|-------|-------|------|
| death                  | 24    | 40    | 0.50 |
| CVD-death              | 9     | 18    | 0.23 |
| MI                     | 8     | 21    | 0.26 |
| stroke                 | 6     | 18    | 0.23 |
| PCI                    | 8     | 13    | 0.16 |
| revascularization      | 6     | 10    | 0.13 |
| amputation             | 6     | 14    | 0.18 |
| all CVD events         | 25    | 48    | 0.60 |
| cancer-death           | 2     | 5     | 0.06 |
| DM nephropathy         | 20    | 37    | 0.46 |
| ESRD                   | 1     | 6     | 0.08 |
| Blindness              | 2     | 7     | 0.09 |
| Progression of DMR     | 41    | 54    | 0.68 |
| Laser or macular edema | 14    | 27    | 0.34 |

| 2-year SURE Study | ≥3 target | <3 targets | HR   |
|-------------------|-----------|------------|------|
| ESRD/death/dSeCr  | 14        | 34         | 0.30 |
| dialysis          | 6         | 12         | 0.11 |
| dSeCr             | 10        | 21         | 0.18 |
| death             | 4         | 15         | 0.13 |
| MI/angina/PCI     | 4         | 7          | 0.06 |
| heart failure     | 12        | 16         | 0.14 |

| 7-year AJMC paper | SC | UC | HR   |
|-------------------|----|----|------|
| death             | 8  | 20 | 0.25 |
| death/CVS/renal   | 20 | 30 | 0.38 |

These Kaplan-Miere plots show the estimated events from these 3 studies in a 2-year period.

Chinese T2D patients with CKD (eGFR 30 ml/min/1.73m^2)  
Chan JC et al Diabetes Care 2009

[figure not shown]

Chinese T2D patients with HT (no CVD/CKD)  
So WY et al Am J Managed Care 2003

[figure not shown][figure not shown]

Caucasian T2D patients with microalbuminuria (no CVD/CKD)  
Gaede P et al NEJM 2008

[figure not shown]

Using validated risk equations and risk parameters, the JADE Program stratified patients into very high risk, high risk, medium risk and low risk groups with respective estimated annual event rate of 7%, 3%, 1.5% and 1%.

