#### Risk levels (5-year event rate)

4: Cardio-renal complications

3: CKD or at least 3 risk factors or high risk score

2: no CKD and 2 risk factors or medium risk score

1: no CKD and 1 or no risk factor and low risk score

Chan JC et al Diabetic Med 2009

In our first year analysis of the JADE Asia Pacific Program, the majority of enrolled patients from 7 countries belonged to very high to high risk category.

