## **DATA ANALYSIS**

All data will be analyzed using the SPSS statistical software (Windows 13.0 version, Chicago, USA). A p value of 0.05 or less (2-tailed) will be considered significant. For the primary composite endpoint, an intention to treat analysis will be performed including all patients randomized to both groups who have at least returned for one visit or contacted by phone once post randomization to ascertain clinical status (alive, dead or hospitalized). Descriptive analysis will be used to report all clinical and laboratory parameters. Student's t-test, Chi-squared test and Analysis of Co-variance will be used for between-group and within-group comparisons for all baseline data and endpoints, as appropriate. Kaplan-Meier curve analysis will be used to compare the incidence of primary composite endpoint between the JADE and DIAMOND group adjusted for age, sex, ethnicity and disease duration. Interaction between group assignment and covariates including age, gender, duration of diabetes (< or ≥8 years), socioeconomic group, complications, risk factors, JADE risk categories, compliance and psychological health parameters will be examined. Logistic regression will be used to determine independent predictors for achieving primary composite endpoint using all relevant covariates including age, gender, duration of diabetes (< or ≥8 years), centre characteristics, socioeconomic group, risk levels, metabolic and risk factor control, compliance, self care, psychological health parameters and intervention groups.

A per protocol analysis will be performed in the JADE group with details of intervention, where we shall compare baseline clinical profile, care processes, number of visits and use of medications between patients who develop and those who do not develop clinical endpoints. A sensitivity analysis will also be performed using hazard rates of the JADE and DIAMOND group amongst those who have defaulted.

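### The primary comparison leaves out baseline JADE risk level, so it is not protected if loss to follow-up depends on risk differently in the two arms

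*Protocol*

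**What the plan says.** The Data Analysis section fixes the adjustment set of the primary comparison. It will "compare the incidence of primary composite endpoint between the JADE and DIAMOND group adjusted for age, sex, ethnicity and disease duration". The same section uses JADE risk level in two other places: as one of several interactions with group, and as one of many covariates, with intervention group, in a logistic model of the primary endpoint. It also plans a sensitivity analysis based on the hazard rates of patients who default, by arm.

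Under Primary composite outcome, the four risk levels, from very high to low, have a "respective estimated annual event rate of 7%, 3%, 1.5% and 1"%. On the expected mix, the protocol says that "the majority of enrolled patients from 7 countries belonged to very high to high risk category"; the figure with the exact shares is not readable.

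On contact, the JADE section says: "Patients randomized to the JADE group will be followed according to the protocol based on their risk levels". Its table recommends 6 or more, 4 or more, 3 or more and at least 2 medical visits a year for the four levels. For the control arm: "Patients randomized to the DIAMOND group will receive usual care after the initial CA with repeat CA at 12 and 24 months". The Objectives describe the two programmes as using the portal "to guide comprehensive assessment with or without risk stratification and clinical protocols", so the control portal is not set up to produce the level.

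**The concern.** Event rates differ seven-fold across risk levels (7% against 1% a year). The protocol quantifies no comparable gradient for age, sex, ethnicity or duration. Omitting such a variable from a randomised comparison is normally harmless. Here there is a documented route by which retention could depend on risk in one arm and not, or less, in the other: JADE contact is graded by risk and control contact is not. The plan allows for 20% attrition. The primary analysis set also requires at least one visit or phone contact after randomisation, so contact affects inclusion as well as censoring.

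If JADE kept its high-risk patients better than the control arm does, its risk set would become sicker over time and a real benefit would look smaller. If the visit burden drove high-risk patients out of JADE, a benefit would look larger or appear where there is none. Adjusting for the four listed covariates would remove only part of either effect.

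**Working it through.** **1. The plan's own figure.** The protocol states no figure for this bias, so its sample size serves as a check on the planning inputs. For 4% against 3.2% at 2 years (HR 0.8), two-sided 0.05 and 80% power, the two-proportion formula gives n = 8,511 per group. With the continuity correction, n/4 × [1 + √(1 + 4/(n × 0.008))]² = 8,760, exactly as tabulated.

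**2. Inputs.** From the protocol: hazards of 0.07, 0.03, 0.015 and 0.01 a year, 2 years, 1:1 allocation, HR 0.80 and about 20% loss. Assumed, because the protocol does not give them: the share of patients at each level, and loss by arm and level. All lists run from very high to low risk. Mix A is 20/45/25/10%. Mixes B are 25/25/25/25%, 30/50/15/5% and 20/40/25/15%.

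**3. Method.** The protocol names Kaplan-Meier curves and no hazard model, so a Cox model stands in for the comparison. Hazards are constant within level and dropout is exponential by arm and level. Let Y_J(t) and Y_D(t) be the expected numbers at risk in JADE and DIAMOND, and e_J(t) and e_D(t) the expected event rates. The large-sample log HR b without risk level solves

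∫ { e_J − (e_J + e_D) × Y_J exp(b) / (Y_J exp(b) + Y_D) } dt = 0.

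No covariates are included, so the results are upper limits on the bias.

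**4. Results without risk level.**

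| Loss over 2 years | Mix | HR if truth is 0.80 | HR if truth is 1.00 |
|---|---|---|---|
| None | B | 0.802–0.803 | 1.00 |
| 20% at every level, both arms | B | 0.802–0.803 | 1.00 |
| Same 10/15/28/35% gradient, both arms | A | 0.802 | 1.00 |
| JADE 15/18/24/28%, DIAMOND 20% | A | 0.812 | 1.01 |
| JADE 10/15/28/35%, DIAMOND 20% | A | 0.822 | 1.03 |
| JADE 5/15/35/45%, DIAMOND 20% | A | 0.837 | 1.04 |
| JADE 5/15/25/35%, DIAMOND 20% | B | 0.820–0.840 | 1.02–1.05 |
| JADE 30/22/13/8%, DIAMOND 20% | A | 0.783 | 0.976 |
| JADE 35/25/15/5%, DIAMOND 20% | B | 0.765–0.781 | 0.95–0.97 |
| JADE 5/15/25/35%, DIAMOND 35/25/15/5% | B | 0.842–0.881 | 1.05–1.10 |

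If JADE 5/15/25/35% against DIAMOND 20% were lost before any contact after randomisation, and so left the analysis set, 0.80 would become 0.84 to 0.88. Stratifying by risk level returns 0.800 and 1.000 in every row, because dropout was assumed to depend only on arm and level.

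**5. Hand check of one null case** (mix A, JADE 10/15/28/35%, DIAMOND 20%), ignoring removal by events. At 2 years the JADE shares still observed are 0.20 × 0.90 = 0.180, 0.45 × 0.85 = 0.3825, 0.25 × 0.72 = 0.180 and 0.10 × 0.65 = 0.065, in total 0.8075. Their mean hazard is (0.180 × 0.07 + 0.3825 × 0.03 + 0.180 × 0.015 + 0.065 × 0.01)/0.8075 = 0.027425/0.8075 = 0.0340. In DIAMOND the mix does not change, and the mean hazard stays at 0.20 × 0.07 + 0.45 × 0.03 + 0.25 × 0.015 + 0.10 × 0.01 = 0.03225. The ratio drifts from 1.00 at entry to 0.0340/0.03225 = 1.05 at 2 years. The average over follow-up is about 1.03, as in the table.

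**6. Power and type I error** at 13,762 randomised (the plan's medium-risk total), mix A. In the three scenarios where JADE keeps its high-risk patients better, power is about 78%, 73% and 65% without risk level, against about 84% with stratification. Two-sided type I error runs from 5.4% to 9.0%. Precision alone gains almost nothing: 54% against 56% power at 6,626 patients, within simulation error.

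**The case against.** A reader might infer that the omission biases the HR as the plan stands. The protocol does not support that. It gives one overall attrition rate and nowhere says that loss depends on risk. The first three rows of the table show that equal loss, or the same risk gradient in both arms, leaves the HR at about 0.80. Only a gradient that differs between arms causes bias, and its direction cannot be predicted.

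The route to such a difference is also weaker than the visit table suggests. Every eligible patient must be willing to return every 3 to 4 months. JADE reviews are elsewhere described without reference to risk: "Patients are booked for reviews led by the doctor-nurse-HCA team every 2-4 months". Comprehensive assessments follow one interval for all JADE levels. Most importantly, outcomes are to be ascertained in all patients at years 1 and 2 and at close-out by phone or interview (Comprehensive assessment, last item). Consent is sought in both arms for contact at least yearly even without a return visit (Default and Missing Data). Fewer clinic visits therefore need not mean censoring for the primary endpoint.

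All of this stands and makes the problem smaller. It does not put risk level into the primary comparison:

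- The plan still allows for 20% loss after these measures.
- The defaulter analysis is by arm, not stated to be by risk level.
- Interaction tests do not adjust the main estimate.
- The logistic model ignores time. It also includes compliance, self care and risk factor control, which the intervention may change, so its group effect cannot replace the primary result.

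Two further limits on the numbers are fair. The 9.0% type I error needs JADE to lose 5% of very-high-risk and 45% of low-risk patients, and the extra rejections go against JADE. The full recovery by stratification follows from the assumption that loss depends only on arm and level.

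**Conclusion.** The point holds as a conditional weakness. The protocol itself lists the covariates of the primary comparison and leaves out the predictor for which it gives a seven-fold gradient. With balanced loss the consequence is negligible: an HR shift of less than 0.003. If loss by risk level differs between arms, a true HR of 0.80 would appear as about 0.81 to 0.84 when JADE keeps its high-risk patients better, or 0.77 to 0.78 when it loses more of them. Only opposite gradients in the two arms, or loss before any contact, give values up to 0.88. These figures rest on assumed risk mixes and loss gradients, and are upper limits because age and duration carry part of the risk level. The change is worth making because it is cheap and protects the result in either direction; bias has not been shown.

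**What to change.** In Data Analysis, add baseline JADE risk level (four levels) as a stratification factor or covariate of the primary time-to-event comparison, next to the four covariates already listed. State that:

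- the level is derived centrally, with one algorithm for every randomised patient, from the baseline comprehensive assessment;
- it is not shown to DIAMOND staff, so that the control condition is unchanged;
- only the baseline value is used. Antihypertensive and lipid-drug treatment count as stratification parameters, so later levels can change because of the intervention.

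The cost is one sentence, one derived variable and a pre-set rule for incomplete inputs, for example a missing category. Such a rule is needed. The protocol accepts total cholesterol and HDL-C alone when fasting is not possible, while the level uses LDL-C and triglyceride. The listed foot examination covers reflexes, pulses and sensation, while the foot-at-risk definition also uses skin changes and deformities. The baseline assessment follows allocation, so the frequency of missing levels should be reported by arm. No extra patients or visits are needed. The change should be made before outcome data are seen.

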#### Complications and risk factors in 3687 Asian T2D patients

[figure not shown]

So WY et al for JADE Study Group J of Diabetes 2011

We used these observations to estimate the sample size needed to give a 2-year study 80% power with an alpha value of 0.05 to confirm the superiority of team-based structured care over usual care on clinical endpoints. We used different combinations of scenarios including an annual hazard rate ranging from 0.01 to 0.10 in the usual care group and a HR ranging from 0.5 to 0.85 in the structured care group with an attrition rate of 0.2, to estimate the sample size. Using the most conservative scenario where the annual hazard rate is 0.02, i.e. 0.04 in 2 years and assuming a HR of 0.8 in the structured care group, the study will have sufficient power to confirm the primary hypothesis. For high risk patients with a hazard rate of 0.05 and those with medium risk (0.03), and assuming a modest HR of 0.8 in the structured care group, a sample size of 6626-13762 patients will give the study 80% power at an alpha value of 0.05.

|                                                     |      |       |                |      |       |       |
|-----------------------------------------------------|------|-------|----------------|------|-------|-------|
| 80% power at 0.05 alpha
minimum 2 year follow up |      |       |                |      |       |       |
| LOW RISK                                            |      |       | VERY LOW RISK  |      |       |       |
| hazard ratio                                        | 0.5  | 0.8   | 0.85           | 0.5  | 0.8   | 0.85  |
| annaul hazard rate                                  | 0.02 | 0.02  | 0.02           | 0.01 | 0.01  | 0.01  |
| hazard rate (usual)                                 | 0.04 | 0.04  | 0.04           | 0.02 | 0.02  | 0.02  |
| hazard rate (structured)                            | 0.02 | 0.032 | 0.034          | 0.01 | 0.016 | 0.017 |
| absolute difference                                 | 0.02 | 0.008 | 0.006          | 0.01 | 0.004 | 0.003 |
| sanple size in each group                           | 1239 | 8760  | 15868          | 2515 | 17838 | 32333 |
| total sample size                                   | 2478 | 17520 | 31736          | 5030 | 35676 | 64666 |
| assuming 20% attrition rate                         | 2974 | 21024 | 38083          | 6036 | 42811 | 77599 |

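### Diabetes duration is split at 8 years without a stated reason in the interaction and predictor analyses, which costs information that a continuous term would keep

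*Protocol*

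**What the plan says.** All of this is in the protocol's Data Analysis section.

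- Interactions with randomised group: "Interaction between group assignment and covariates including age, gender, duration of diabetes (< or ≥8 years), socioeconomic group, complications, risk factors, JADE risk categories", and then "compliance and psychological health parameters will be examined". Nine items are named. Several are plural and the list is open-ended, so nine is a minimum.
- Logistic model for predictors of the primary composite endpoint: "using all relevant covariates including age, gender, duration of diabetes (< or ≥8 years), centre characteristics, socioeconomic group, risk levels", followed by further items. The 8-year split appears here again.
- Adjusted comparison of the primary composite endpoint: "adjusted for age, sex, ethnicity and disease duration". Duration is named without any coding.
- Decision rule: "A p value of 0.05 or less (2-tailed) will be considered significant". It is stated once, for all analyses.

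The protocol gives no reason for choosing 8 years. It gives no mean, median, spread or share of patients on either side of the cut. The inclusion criteria admit both newly diagnosed and established disease, so duration starts at zero and may extend over many years.

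**The concern.** A two-group split treats a newly diagnosed patient and one at 7.9 years as the same, and treats 7.9 and 8.1 years as different. If the benefit of structured care changes gradually with duration, the split weakens the test for that change. In the predictor model, whatever duration explains within each half is left unadjusted. It can be picked up by covariates that move with duration, such as risk level or metabolic control.

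What is at stake is the power of one interaction test and the quality of adjustment in one secondary model. The coding is written into the protocol, so this is not a detail that the protocol leaves open.

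**Working it through.** **Inputs.** The protocol supplies the 8-year cut, the two-sided 0.05 threshold and the nine named interaction items. The shape of the duration distribution and a linear effect are assumptions, because the protocol gives neither.

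**The plan's own figures.** The protocol states no information loss and no power for interactions. Its only power statement on clinical endpoints is for the main comparison: "80% power with an alpha value of 0.05 to confirm the superiority of team-based structured care over usual care on clinical endpoints". That convention reproduces. For 0.04 against 0.032, the two-proportion formula at 80% power and two-sided 0.05 gives 8511 per group, or 8760 with the continuity correction. The low-risk table gives 8760. I therefore use 80% at 0.05 as the benchmark; the protocol does not promise it for an interaction.

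**Step 1, information kept.** For a linear effect, the share kept by a split is the squared correlation between the covariate and its two-group indicator. For a normal covariate with a proportion p below the cut c,

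share kept = φ(c)² / [p(1 − p)].

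At the median: 0.3989² / 0.25 = 0.637, so the loss is 36.3%.

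| Assumed shape of duration | Information lost |
|---|---|
| Normal, 50/50 split | 36% |
| Normal, 35/65 split | 40% |
| Normal, 30/70 split | 42% |
| Normal, 20/80 split | 51% |
| Uniform, 0–16 or 0–20 years | 25–28% |
| Gamma (shape 2), mean 6–12 years | 36–54% |
| Exponential, mean 6–12 years | 36–53% |
| Log-normal, median 6–10 years, log-SD 0.8 | 54–71% |

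The last four rows were simulated with the cut at 8 years.

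**Step 2, effect on power.** A test with 80% power has an expected Z of 1.96 + 0.84 = 2.80. After the split,

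power = Φ(2.80 × √(share kept) − 1.96).

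- 25% lost: Φ(2.80 × 0.866 − 1.96) = 68%
- 36% lost: Φ(2.80 × 0.80 − 1.96) = 61%
- 40% lost: Φ(2.80 × 0.775 − 1.96) = 58%
- 71% lost: Φ(2.80 × 0.54 − 1.96) = 33%

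Equivalently, recovering the lost power would take 1/(1 − loss) times the patients: 1/0.64 = 1.6 times at 36%, with a range from 1/0.75 = 1.3 to 1/0.29 = 3.4.

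**Side check, number of interactions.** If nine independent tests were each read at 0.05, the chance of at least one false positive would be 1 − 0.95⁹ = 37%. It passes one half only at 14 tests (1 − 0.95¹⁴ = 51%; 13 tests give 49%).

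**The case against.** The best defence is that the cut is fixed in advance. That prevents a threshold being chosen after seeing the data, and a two-group display is easy to read. The affected analyses are secondary. This stands and keeps the point minor. It does not justify the split, since a continuous term written into the protocol is equally pre-specified and keeps the information.

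It is also fair to say that the trial is not sized for interactions. With an even split, an interaction as large as a main effect powered at 80% has power of only Φ(1.40 − 1.96) = 29%. That weakness belongs to any 50:50 subgroup and is not caused by the cut. The 80% starting point is therefore a benchmark, but the relative loss applies whatever the starting power.

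Several stronger readings are tempting and are not supported:

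- *A fixed loss of about 40%.* The protocol gives no distribution for duration, so only a range under stated assumptions can be given.
- *Duration is coded in two conflicting ways.* The primary comparison names duration without a coding. Silence is not a second coding.
- *The split confounds the trial result.* Group is randomised, so coarse coding of a baseline covariate does not confound the treatment effect or its interaction with duration. Residual confounding concerns the other predictors in the logistic model.
- *A false subgroup finding is likely.* The 37% is below one half and assumes independence. Risk category is itself built from complications and risk factors (section on the JADE group intervention), so the tests are correlated and the chance would usually be lower.
- *Each interaction will be declared at 0.05, and the results decide who benefits.* The text says only that interactions will be examined. The Objectives and Hypothesis sections make no subgroup claim. Adjusting these tests or naming a lead interaction is commonly left to a statistical analysis plan, which is not shown here.

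**Conclusion.** The point holds as a cheap improvement, not as an error that threatens the trial. The protocol fixes an unexplained 8-year split of duration in two analyses. For a roughly linear effect and a near-normal distribution cut at its median, about 36% of the information is lost, and 80% power for a treatment-by-duration interaction becomes about 61%. Over the other assumed shapes the loss is about 25% to 71% and the power 68% to 33%. If the effect were truly a step at 8 years, the split would lose nothing, but the protocol offers no reason to expect one.

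The power loss concerns duration only, one of the nine listed items. The primary randomised comparison, as written, does not use the split. The number of interactions is a side note: it warrants a label and cautious reporting, and is not a separate defect in the protocol as it stands.

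**What to change.** In the Data Analysis section, enter diabetes duration as a continuous term, linear or as a pre-specified spline, in both the interaction analysis and the logistic predictor model. Keep the split at 8 years for tables and figures only. If it must stay in a model, give the reason for the cut.

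Alongside this, add a sentence labelling the listed interactions as exploratory, to be reported as estimates with 95% intervals.

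The cost is a change of wording, provided that duration is captured in years or can be derived from the date of diagnosis; the 8-year cut implies this, but the protocol does not state the format. The small downside is a less simple presentation, since an interaction with a continuous variable needs a plot or estimates at chosen durations in place of two subgroup rows.
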